**Study Design**

This is a cohort study to categorise the traumatic brain injury population at UHB. Brain biomarkers, serum, micro-diasylate, CSF and imaging will be measured in two groups of patients. Outcome will be assessed by TMS threshold, ERP, ERG, VEP and cognitive and psychological questionnaires will be performed. The two groups of patients will be:

The study group - patients who have suffered a head injury presenting or transferred to UHB.

The control group - patients admitted with non-head trauma matched to the study group by ISS severity and demographic.

Patients for inclusion will be identified at point of injury or as soon as possible after presentation to UHB upto 1 hour post injury. For samples taken pre-hospital where patients are unable to consent these will be taken, subject to a favourable REC opinion under the Mental Capacity Act ‘waiver’ for research in emergency situations. Advice will be sought from a consultee as soon as practicable following presentation to hospital and consent will be sought from the patient once capacity has been regained. Information in the form of the included Patient Information Sheets or Consultee Information Sheet will be provided; consent or advice will be recorded on the appropriate written forms annexes c-i.

*Inclusion criteria:*

Study group - Patients who have sustained a head injury resulting in presentation to UHB within 1 hour of injury.

Control group - non-head trauma patients matched to control by severity (ISS) and demographic.

*Exclusion criteria:*

Children under the age of 18 years. For the control group those with a recent head injury or known neurological condition.

Our conservative assumption is that 80% of head injured patients will show a positive biomarker response with 10% of non-head injured patients showing a positive response. Using fishers Exact test (power0.9; alpha 0.05; 1:1 control subject ratio) would predict 10 patients in each group. However head injuries and trauma in general demonstrates much heterogeneity and to allow comparison across modalities and sub-groups we intend to recruit up-to 100 patients to the study group and the control group.

*Sampling - Blood*

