**Methodology**

1. Patient Recruitment: All trauma patients with a survivable injury and ISS (decision) will be entered into the study. 100 trauma patients with a brain injury and 100 trauma patients without a brain injury will be studied. The study team will liaise with the emergency department at UHB for local trauma.
   1. Patient journey: Demographics will be entered into a patient database, a schedule of sampling will then be generated to allow the patient to be followed through the study.
   2. Insults: initial injury and insults - baseline GCS score, post-traumatic amnesia, surgical intervention, infection, sepsis, ICP, cerebral blood flow and oxygenation, seizure.
   3. Timings: Admission, surgery, ventilation days, ICU days, discharge, rehabilitation, time to recovery.
2. Measurements and sample collection: The following measurements will be made on samples taken from point of injury through to six month follow-up. The schedule appears in table 1.
   - 1. *Venous blood*. Venous access for drugs and fluids is gained early in trauma care at point of injury, however blood would not routinely be withdrawn as there are no useful clinical tests at this stage currently. We propose to withdraw 20mls at this point for analysis of the early biomarker milieu. An additional 20mls of venous blood will be taken at subsequent time-points. These will be analysed for biomarker levels and metabolomics. Genomic analyses will be carried out on mitochondrial and nuclear DNA, including mitochondrial DNA haplogroups, Apoliprotein E haplotypes and genes of the MToR pathway.
   1. *Micro-diasylate*. Micro-dialysis is used in routine clinical practice to monitor cerebral perfusion. The small amount of diasylate generated would normally be discarded in clinical practice, we propose to recover it for analysis. The diasylate will be snap frozen following recovery and sent to DSTL for analysis.
   2. *CSF*. Where CSF is withdrawn in normal clinical practice an additional 5 mls will be withdrawn for biomarker analysis.
   3. *Imaging.* MRI, MRS, DTI, will be performed in accordance with the schedule at table 2.
      1. MRI: T1, T2, FLAIR, DWI, ADC sequences will be acquired on a 1.5T scanner in the UHB inpatient imaging department.
      2. MRS: sequences will be acquired on a 1.5T scanner in the UHB inpatient imaging department.
      3. DTI: sequences will be acquired on a 1.5T scanner in the UHB inpatient imaging department.

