   2. Routine blood analysis will be performed as per normal clinical practice by UHB haematology and biochemistry laboratories.
   3. Biomarker assays will be performed at DSTL and UoB.
   4. Genomic analyses will be carried out at UoB
   5. MRI Imaging will be performed in the inpatient MRI department, UHB.
   6. Trans-cranial Magnetic Stimulation, EEG and TOMM will be conducted in the outpatients neurophysiology department of UHB.

Table 1. Schedule of sample analysis

| Time | Sample | Measurement |
| --- | --- | --- |
| 0 (point of injury) | 20mls venous blood | Biomarkers analysis |
| Day 1 (UHB ED) (if no point of injury sample taken) | 20mls venous blood | Biomarkers analysis |
| Day 1 (6-12hrs post injury) | 20mls venous blood | Biomarkers analysis |
| Day 3 | 20mls venous blood | Biomarkers analysis |
| Day 1-14 | Micro-diasylate  CSF (if available) | Biomarkers analysis |
| Day 180 (+/-30) | 20mls venous blood | Biomarkers analysis, Genetic analysis |

Table 2. Schedule of Imaging

| Time | Imaging | Notes |
| --- | --- | --- |
| Day 1-30 | MRI or MRS or DTI | Random selection of patients once stable |
| Day 180 (+/-30) | MRI or MRS or DTI | Same modality as before for comparisom |
| Day 360 (+/-30) | MRS | If 180 day MRS scan abnormal |

Table 3. Schedule of Outcome Measures

| Time | Measures | Notes |
| --- | --- | --- |
| Day 1-30 | Pupillometry | Where possible |
| Day 180 (+/-30) | Cognitive/psychological questionnaires |  |
| Day 360 (+/-30) | Cognitive/psychological questionnaires  TMS  ERP |  |

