**Outcome Measures**

Outcome of brain trauma will be assessed with cognitive and psychological symptom scoring, TMS threshold measurement and ERP. Initial severity scoring will be assessed with ISS/NISS. Changes in biomarkers will be measured in relation to brain trauma versus non-brain trauma and related to the above outcome assessment.

The primary outcome will be functional status as measured by the Glasgow Outcome Score at 6 months. Secondary outcome measures are functional status as assessed by the Glasgow Outcome Score at 12 months; cognitive and psychological symptom scoring with Post­concussion Symptom Questionnaire­19 (PCSQ­19), Impact of Events Scale – revised (IES­r), Depression and Anxiety Symptom Scale – 21 (DASS­21), PTSD checklist (PCL), Patient Health Questionnaire (PHQ), neurological assessment battery NAB-SM.

Other seconday outcome measures are neurophysiology measures of TMS threshold and Event related potentials.

Developing a better understanding of the relationships surrounding severe brain trauma and biomarkers in development will lead to better clinical understanding, categorisation, prognostication and treatments, both in targeting existing interventions and through development of new treatment in future interventional studies.

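### The Glasgow Outcome Score at 6 months is declared the primary outcome, but the outcome schedule and every other outcome or measurement list in the protocol omit it, so it may not be collected on time.

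*Protocol*

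**What the plan says.** The Outcome Measures section that follows Statistical Analysis names the primary outcome: "The primary outcome will be functional status as measured by the Glasgow Outcome Score at 6 months". It continues: "Secondary outcome measures are functional status as assessed by the Glasgow Outcome Score at 12 months; cognitive and psychological symptom scoring with", and then names six instruments: PCSQ-19, IES-r, DASS-21, PCL, PHQ and NAB-SM. TMS threshold and event-related potentials follow as further secondary measures.

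Other parts of the protocol describe the outcome set without the Glasgow Outcome Score (GOS):

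- Study Design: "Outcome will be assessed by TMS threshold, ERP, ERG, VEP and cognitive and psychological questionnaires".
- Table 3, 6 months: "Day 180 (+/-30) | Cognitive/psychological questionnaires".
- Table 3, 12 months: "Day 360 (+/-30) | Cognitive/psychological questionnaires TMS ERP".
- The opening sentence of the declaring section itself: "Outcome of brain trauma will be assessed with cognitive and psychological symptom scoring, TMS threshold measurement and ERP".

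**The concern.** A primary outcome has to appear where the protocol says what is measured and when. Here it appears only where it is declared. Table 3 is titled as the schedule of outcome measures, so staff could reasonably plan the 6- and 12-month contacts from it. If they did, they would collect questionnaires and neurophysiology but no rating of functional status.

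The main hypothesis relates biomarkers after trauma to outcome at 6 and 12 months, and the protocol criticises earlier studies for limited outcome assessment. If the GOS were not rated at the time, the prognostic analysis would fall back on the secondary measures. Those need a patient who is alive and able to complete a questionnaire or a test session, so the fallback would tend to leave out the worst outcomes. A functional rating can include those patients.

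**Working it through.** This point involves no arithmetic on a stated figure. The protocol's sample-size calculation concerns a positive biomarker response (80% against 10%), not the GOS, so nothing in it depends on this point. The check is a comparison of every place where the protocol lists outcomes, measurements or analysis variables.

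**Where the GOS appears.** Outcome Measures (after Statistical Analysis), second paragraph: at 6 months as primary, at 12 months as secondary.

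**Where it could be expected but does not appear.**

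1. *Study Design, outcome sentence.* Lists TMS threshold, ERP, ERG, VEP and questionnaires.
2. *Study Design, outcome narrative* (the subsections on outcome measures, questionnaires and neurophysiology). Covers questionnaires, TOMM, NAB, TMS, P300, VEP and ERG.
3. *Methodology, item 2.* It opens: "The following measurements will be made on samples taken from point of injury through to six month follow-up". The list then runs through blood, micro-dialysate, CSF, imaging, TOMM and NAB, TMS, EEG, ERG, VEP and pupillometry. The only Glasgow scale in Methodology is the baseline GCS in item 1, which is recorded as part of the initial injury and is a different scale.
4. *Methodology, Table 3.* Three rows: pupillometry in Days 1-30; questionnaires at Day 180; questionnaires, TMS and ERP at Day 360. None has the GOS.
5. *Statistical Analysis, primary dependent variables.* Biomarker levels, imaging, TMS threshold and cognitive/psychological scoring.
6. *Outcome Measures, opening sentence.* Cognitive and psychological scoring, TMS threshold and ERP.

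**Could the questionnaire rows of Table 3 include the GOS?** Two passages say otherwise. The secondary-outcome sentence treats functional status by GOS as one item and cognitive and psychological scoring as another, and lists the instruments under the latter; the GOS is not among them. The questionnaire subsection of Study Design limits the questionnaires to cognition and memory, post-traumatic stress, depression and anxiety. Functional status is not mentioned.

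**Could it come from routine care?** Ethical Considerations refers to questionnaires used in routine practice, but only as one part of cognitive and psychological scoring. The protocol does not say that the GOS is routinely recorded in either group.

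**What time window is at stake?** If the GOS takes the windows of Table 3, the 6-month rating falls between 180 - 30 = Day 150 and 180 + 30 = Day 210, and the 12-month rating between 360 - 30 = Day 330 and 360 + 30 = Day 390. A rating omitted at those contacts would have to be made later or reconstructed.

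**The case against.** The strongest reply is that neither the schedule nor the measurement list is exhaustive. Methodology places ERG and VEP at 1 year, yet Table 3 has neither. The measurement list also leaves out PCSQ-19, IES-r, DASS-21, PCL and PHQ, all of which are named outcomes. The declaring section belongs to the same protocol and fixes both the instrument and the times. What staff actually work from cannot be established: the Annexes list instructions for the research team, whose text is not available here, and Methodology says that a sampling schedule is generated for each patient from the database. Statistical Analysis introduces its dependent variables with an open-ended verb and plans an ordinal analysis of outcome, which would suit a graded scale.

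Much of this stands, and it limits the conclusion to a risk. It does not remove the contradiction. ERG and VEP are missing from Table 3 but have their own measurement entries with a time. The named questionnaires are missing from the measurement list but are covered by a Table 3 row. The GOS has neither. The ordinal analysis names no scale and cannot create a data-collection step. Nor is this detail that an SAP would supply, because what is measured at each contact belongs to the protocol.

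A reader might go further and infer that none of the planned 200 patients would have a primary outcome. The documents do not support that. The count only restates the omission as a number. It treats Table 3 as the controlling list and assumes that all 100 controls are due a GOS, although the declaring section introduces its measures as outcomes of brain trauma and does not mention controls. Study Design also gives 100 per group as an upper limit. A reader might likewise assume that clinical notes could not yield the grades; the protocol says nothing about that.

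**Conclusion.** The contradiction is established from the text. The primary outcome is declared in one section and omitted from six other places, one of them the opening sentence of that same section, and the questionnaire rows of Table 3 do not cover it. Two outcome sets stand side by side and must be reconciled.

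The consequence is a risk that the primary outcome is not collected within its window. Its size cannot be calculated, because it depends on what staff use as their working schedule, and the documents do not show that. The conclusion assumes only that Table 3 may be used as it is titled and that no unseen annex adds the GOS. The choice of the GOS at 6 months is not criticised, and the sample size is unaffected.

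**What to change.** 1. Add the GOS to Table 3 at Day 180 (+/-30) and Day 360 (+/-30), and to the measurement list in Methodology item 2.
2. State whether it applies to both groups or to the head-injury group only.
3. When a patient does not attend, obtain it through the telephone contact that Ethical Considerations already provides for. Record deaths in the GOS category for death.
4. Align the outcome sentence in Study Design, the primary dependent variables in Statistical Analysis, and the first paragraph of the Outcome Measures section.

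The cost is a line in the table, a field on the case-report form and a short rating at contacts that are already scheduled. No extra visit or clinic procedure is needed.

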**Ethical Considerations**

In the initial phases of management it will be very challenging to obtain informed consent due to the nature of the injuries both in brain and non-brain trauma. Inherent in the severity of these injuries patients will frequently lack capacity under the Mental Capacity Act (MCA)2005. In the emergency setting a sample will be withdrawn from patients unable to consent under the MCA ‘waiver’ for research in emergency situations, subject to a favourable REC opinion. As soon as practicable and once a patient has been assessed under section 3 of the MCA the study team will seek the advice of a consultee prior to entry into the study (this will be under the terms of Section 32 and 33 of MCA 2005). Once capacity has been regained consent will be sought from the patient prior to continuation in the study.

The risks of participation in the study are minimal. The burden will be greatest physically and psychologically late in the study during rehabilitation.

Blood sampling is a routine aspect of hospital care. The drawing of samples will where possible be taken additionally to routine sampling of clinical necessity. At point of injury sampling will only take place where venous access has been placed for clinical reasons. Later in the study sampling will be performed where there is no clinical need. This will present minor discomfort to the participant. All sampling will be conducted by medical personnel well trained in the procedure with care taken to minimise discomfort.

Micro-dialysis is a routine aspect of care for head injuries at UHB. Currently the diasylate has no clinical use and is disposed of. Where micro-dialysis has been utilised for routine clinical treatment we propose to recover the diasylate for research analysis. CSF studies are occasionally performed for clinical reasons. Where these take place we propose to withdraw and additional 5mls for research purposes. Neither of these samplings would introduce an additional burden.

Imaging is a routine part of trauma care however at present CT scanning is the standard at initial assessment and following clinical changes that so warrant it. During the initial 1-4weeks of the hospital stay and following discharge from ITU participants will be randomised to an imaging modality and will undergo an additional scan. This will either be MRI using conventional sequences, MRS or DTI. Requirements for scans would not be in excess of the burden of normal MRI clinical scanning, there is no ionising radiation exposure and no known health concerns from exposure to magnetic fields. Exclusion criteria for exposure to magnetic fields will be applied as for clinical scanning. Scans would be repeated at 6 months using the same modality, and additionally at 1 year where 6 month MRS scans are abnormal.

Trans-cranial Magnetic stimulation is a neurophysiological technique that allows the induction of a small current in the brain to excite its neurons. It uses a magnetic field to pass through the scalp and the skull safely and painlessly. This technique, when conducted in accordance with internationally recognised guideline, is safe and is part of standard clinical tests in neurology in many countries worldwide. All participants will be screened for contraindications to TMS using a validated questionnaire for healthy participants that we have modified for traumatic brain injury (Annex k).

Electro-encephalogram and event related potential is a technique using conventional EEG recording in the setting of provision of controlled stimuli with the intent of measuring the p300 potential. The participant has an EEG recorded whilst undertaking a task with an audible odd-ball paradigm. This challenges the person with and unexpected ‘noise’ and the EEG records the cortical response. Changes in the timing of the well categorised p300 potential give us insight into the presence of damage in the sub-serve neural pathways.

Cognitive and psychological symptom scoring will be conducted in two parts. The first are a range of questionnaires used in routine practice. At follow-up a trained clinical psychologist will administer the remaining tests, TOMM and NAB, verbally.

Every effort will be made to take samples during procedures for clinical necessity, additional samples and testing will be timed to coincide when called for clinical follow-up. The testing will be accomplished in a single visit. There will however be occasions where patients would be lost to follow-up should they not be called in to allow testing and sampling. These instances will be minimised. Reasonable travel and parking costs will be reimbursed. Participants will be contacted via telephone, letter of email as per their preference following hospital discharge.

The study will be conducted in accordance with this protocol and Good Clinical Practice. The study complies, and will at all times comply, with the Declaration of Helsinki as adopted at the 52nd WMA General Assembly, Edinburgh, October 2000; and with the Draft Additional Protocol to the Council of Europe Convention on Human Rights and Biomedicine on Biomedical Research (CDBI/INF (2001) 5 dated 18 July 2001).

**Documentation**

All study documents appear at the end of this document.

Participant’s General Practitioners will be informed of participation in this study through the GP Letter, to include the Participants’ Information Leaflet.

**Publication**

Results will be published in peer-review journals and presented at relevant scientific meetings. All participants shall receive a short report of the study findings.

**Annexes**

1. Instructions for research team.
2. Guidelines for blood sampling.
3. Participant Information sheet - TBI. Dated 27 December 2013.
4. Participant Information sheet - continue in study. Dated 27 December 2013.
5. Participant Information sheet - Control. Dated 27 December 2013.
6. Consultee (Next of Kin) Information Sheet. Dated 27 December 2013.
7. Consent form for participants. Dated 27 December 2013.
8. Consent form for participants – continue in study following consultee advice. Dated 27 December 2013.
9. Record of Consultation for Consultee (Next of kin) of Participants Dated 27 December 2013.
10. GP information letter. Dated 27 December 2013.
11. Trans-cranial Magnetic Stimulation safety questionnaire.
12. Psychologist administered TOMM score sheet.
13. Participant Information Sheet - Supplement. Dated 27 December 2013.
